**Methods/design:**

A randomized multi-center controlled trial will be conducted in Germany, comparing supervised aerobic and resistance training 2x/week (13th to 36th weeks of gestation) and nutritional counseling (6th to 36th weeks of gestation) during pregnancy with usual care. Thirty women (pre-pregnancy Body Mass Index ≥25 kg/m^2^, 6th–10th week of gestation) will be included in each group. Maternal anthropometric and physical measurements as well as blood sampling will occur at the 6th–10th, 13th–14th, 21st-24th, and 36th week of gestation, at delivery as well as 8 weeks and 24 months postpartum. Neonatal measurements and umbilical blood sampling will be performed at birth. Maternal and infants’ weight development will be assessed every 6 months till 24 months postpartum. A difference in childhood BMI of 1 kg/m^2^ at the age of two years between both groups will be assumed. A power size of 80% using a significance level of 0.05 and an effect size of 1.0 is presumed.

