## Background

The prevalence of overweight (Body Mass Index ≥25 kg/m^2^) and obesity (Body Mass Index ≥30 kg/m^2^) is increasing worldwide in every age group [1]. In Germany, the number of obese women of child-bearing age has increased especially over the last 25 years from 8.1% in 1990/1991 (25–34-year-old women) to 17.3% (30–44-year-old women) in 2014/2015 [2–4]. When obese women become pregnant they are at increased risk of several perinatal and postpartum complications such as excessive weight gain, gestational diabetes, preeclampsia, pregnancy-induced hypertension or fetal macrosomia [5, 6]. In addition, maternal overweight, excessive weight gain, and gestational diabetes during pregnancy are associated with obesity in childhood and adolescence in the child [7, 8]. Furthermore, children of overweight mothers are at increased risk for long-term metabolic dysfunctions such as hypertension, insulin resistance or metabolic syndrome [8, 9].

Epidemiological, clinical (animal), and experimental studies suggest that maternal lifestyle during pregnancy influences the metabolic, pro-inflammatory, and neurotropic pattern of the unborn child [10–12]. For instance, lifestyle factors have shown to affect adipokines, namely leptin, resistin and adiponectin as well as cytokines such as tumor necrosis factor alpha (TNF-α) and interleukin 6 (IL-6) [13, 14]. These, in turn, are involved in the regulation of maternal metabolic homeostasis and glucose metabolism, and the development of insulin resistance, metabolic syndrome, gestational diabetes mellitus, and hypertension [13].

Reports show that dietary patterns are associated with adiponectin, leptin, and insulin resistance [14–16]. For example, high intakes of fat are negatively associated with adiponectin levels and positively associated with leptin concentrations during pregnancy [16].

However, there are few reports about the interplay of lifestyle factors, in particular maternal exercise, during pregnancy and their effects on biomarkers in mother and offspring [17, 18].

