### Participants

#### Inclusion and exclusion criteria

Women with a pre-pregnancy BMI [35] of ≥25 kg/m^2^, a singleton pregnancy, and a gestational age between 6 and 8 weeks, who were previously sedentary, are without pre-existing conditions such as heart disease, and who are currently not consuming alcohol or using medication for mental health disorders, will be recruited. At 13 weeks of pregnancy, women will receive a physician’s clearance to participate in physical activity. For further participation, they should have no contraindications to exercise during pregnancy according to the American College of Obstetrics and Gynecology [36]. Women with pre-existing diabetes, hypertension, or comorbidities known to affect fetal growth will be excluded from the study as well as women who are not proficient in German. Monthly obstetric check-ups will ensure maternal and fetal well-being.

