#### Secondary outcomes

Secondary outcomes will be assessed during pregnancy and postpartum and will include:
The course of pregnancy (weight gain according to the recommendations of the Institute of Medicine (IOM) [45], manifestation of pregnancy-induced diseases, mode of delivery)Anthropometric data of the mother and the father (weight, height, BMI, circumferences, body fat distribution)Anthropometric data and health status of the new-born (birthweight, length, head circumference, umbilical artery pH value, Apgar scores at one, five and ten minutes)Cord blood biomarkers in the newborn (insulin, leptin, adiponectin, resistin, BDNF, TNF-α, IL-6, CRP, fetuin A)Maternal and paternal biomarkers (insulin, leptin, adiponectin, resistin, BDNF, TNF-α, IL-6, CRP, fetuin A) during and after pregnancyMaternal cortisol level in the saliva at mid-pregnancyPostnatal depression (using the Edinburgh Depression Scale) 8 weeks after birthInfant development (age-appropriate development of fine and gross motor skills, communication, personal and social skills)

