#### Statistics

The main variable (BMI at 24 months) will be analyzed by covariance analyses evaluated by the factor group, breastfeeding, and smoking as well as covariances of parental age, paternal BMI, socioeconomic status, breastfeeding, and potential pregnancy-induced diseases (e.g. gestational diabetes mellitus, pregnancy-induced hypertension (PIH)). The significance level alpha will be set at < 0.05 for all analyses. All confidence intervals will be estimated at 95%. Missing data will be calculated according to the LVCF approach (Last Value Carried Forward). Analyses will be carried out as per-protocol-analyzes and intention-to-treat analyses (ITT). Spearman and Pearson correlation procedure will be used to assess relationships between maternal data (physical activity in METs, eating habits, weight gain, blood samples) and neonatal data (birth weight, length, head circumference, Apgar scores, cord blood sample) as well as infants’ development. Multiple linear regressions will be performed for neonatal measures to determine correlations with maternal and paternal lifestyle factors. The model will include group (intervention yes/no) as well as maternal and paternal characteristics as possible confounders. Explained variance (r-squared) for the linear regression model will be reported as model fit statistic.

Statistical analysis will be performed using SPSS 24.0 data-analysis software (Statistical Product and Service Solutions 24.0) and data analysis will be blinded.

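### The primary ANCOVA adjusts for gestational diabetes, pregnancy-induced hypertension and breastfeeding, which arise after randomisation, so it may not estimate the programme's total effect on infant BMI

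*Protocol article*

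**What the plan says.** The Statistics section specifies the primary model: "The main variable (BMI at 24 months) will be analyzed by covariance analyses evaluated by the factor group, breastfeeding, and smoking". It then lists covariates: parental age, paternal BMI, socioeconomic status, "breastfeeding, and potential pregnancy-induced diseases (e.g. gestational diabetes mellitus, pregnancy-induced hypertension (PIH"). Breastfeeding therefore appears once as a factor and once as a covariate. The article describes no analysis of the primary outcome without these terms. Both per-protocol and intention-to-treat analyses are planned.

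Four other places bear on the point:

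- **Inclusion and exclusion criteria:** "Women with pre-existing diabetes, hypertension, or comorbidities known to affect fetal growth will be excluded from the study".
- **Abstract, Methods/design:** the exercise part is "supervised aerobic and resistance training 2x/week (13th to 36th weeks of gestation"). The dietary part, with the comparator, reads "nutritional counseling (6th to 36th weeks of gestation) during pregnancy with usual care". The Nutrition counseling section adds a last group session 8 weeks after birth.
- **Secondary outcomes:** the course of pregnancy includes "manifestation of pregnancy-induced diseases, mode of delivery".
- **Background:** lifestyle is said to affect adipokines and cytokines that play a part in gestational diabetes and hypertension. Maternal overweight, "excessive weight gain, and gestational diabetes during pregnancy are associated with obesity in childhood" and adolescence.

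The Discussion gives the main aim as finding out whether exercise and nutritional counselling in pregnancy affect infants' BMI and development at two years. It does not restrict the question to an effect that bypasses the course of pregnancy or infant feeding.

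**The concern.** Adjusting for a variable that was fixed before randomisation gains precision and leaves the target of a linear model unchanged. Adjusting for a variable that the intervention can alter does not share that property. The group coefficient then compares the arms as if that variable were held equal, which takes out whatever part of the effect runs through it. If an unmeasured factor influences both the variable and child BMI, conditioning on the variable also opens a non-randomised path between group and outcome. The coefficient is then neither the total effect nor a clean direct effect.

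What is at stake is the meaning of the primary result. The trial asks whether a changed fetal environment alters child weight, and gestational diabetes is one of the ways in which the Background says the fetal environment and child weight are connected. A primary model that holds it constant sets aside part of the mechanism under test.

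**Working it through.** **1. Do the covariates arise after randomisation?** Women enter in early pregnancy, and pre-existing diabetes and hypertension are exclusions. Any gestational diabetes or PIH in the model must therefore appear after entry, while the programme is running. Breastfeeding starts only after birth. The week of randomisation is not given, but it must precede arm-specific counselling in early pregnancy. The timing is certain for all three.

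**2. Does the document place them on the causal path?**

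| Variable | Programme may change it | It may change child BMI |
|---|---|---|
| Gestational diabetes | Yes: secondary outcome, and Background (lifestyle-sensitive markers) | Yes: Background (association) |
| PIH | Yes: secondary outcome, and Background (hypertension) | Plausible, not stated |
| Breastfeeding | Plausible, not stated (counselling continues to 8 weeks postpartum) | Not stated; implied only by its use as an adjustment variable |

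Both links are written down only for gestational diabetes.

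**3. The plan's own power figure.** The Sample size section gives a difference of 1 kg/m², effect size 1.0, alpha 0.05, power 80% and 48 women. Read as a standardised mean difference, this implies SD = 1/1.0 = 1.0 kg/m². A two-sided two-sample t-test at d = 1.0 needs 17 per arm (34 in total) for 80% power. With 24 per arm the power is 92.4%, so the stated 80% is not reproduced. That is a separate matter; 92% serves below only as the reference for 48 infants.

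**4. Illustration of size (assumed shares).** Let the total effect be 1.0 SD and let a share m run through the adjusted variables, in the same direction as the rest. Ignoring shared causes, the adjusted coefficient targets 1.0 × (1 − m). Power is from the two-sided t-test at 0.05 with 24 per arm.

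| m | Coefficient targeted (SD) | Power |
|---|---|---|
| 0 | 1.0 | 92% |
| 20% | 0.8 | 77% |
| 30% | 0.7 | 66% |
| 40% | 0.6 | 53% |

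Nothing in the document fixes m. The formula also ignores any variance that the covariates explain.

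**5. Illustration of shared causes (simulation, all values assumed).** The direct effect is −0.80, a binary mediator raises BMI by 1.0, and one unmeasured factor drives both mediator and BMI.

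| Mediator rate, control → intervention | Total effect | Adjusted coefficient |
|---|---|---|
| 27% → 27% (no programme effect) | −0.80 | −0.80 |
| 27% → 14% | −0.92 | −0.75 |
| 27% → 6% | −1.00 | −0.72 |

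The totals agree with direct effect plus change in rate times 1.0; for the second row, −0.80 + (0.142 − 0.267) × 1.0 ≈ −0.92. In the last two rows the adjusted coefficient misses the total effect and also the direct effect of −0.80. In the first row nothing is lost.

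**6. The double entry.** The factor list reads "evaluated by the factor group, breastfeeding, and smoking", and breastfeeding returns among the covariates. If both are coded alike, the second term is redundant and the group coefficient is unaffected. If they are coded differently (for example ever/never and duration), the coding is not stated.

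**The case against.** - **Breadth.** The Background sentence on childhood obesity names maternal overweight, weight gain and gestational diabetes, and speaks of association only. It does not name PIH, and no passage says that the programme alters breastfeeding. This stands: support in the text is full for gestational diabetes and partial for the other two.
- **Direction.** A reader might infer that the result will be attenuated. The document does not support that. It requires an indirect effect of the same sign as the direct one and no offsetting shared causes, and if the programme changes none of these variables there is no distortion from this source.
- **Magnitude.** A reader might take the power figures as expected losses. They rest on assumed shares. In the simulation a fall from 27% to 14% moves the coefficient from −0.92 to −0.75, a difference of 0.17/0.92 ≈ 18%, just below the range used in the illustration. A simple t-test also leaves out the precision that covariates bring: at a coefficient of 0.7 SD, if covariates explained 10–30% of the variance (assumed; lost degrees of freedom and correlation with group ignored), power would be about 71–81% rather than 66%.
- **Drop-out criteria.** Women with pregnancy complications are to be excluded. If that covers gestational diabetes and PIH, these covariates would be nearly constant in the per-protocol set and adjustment there would matter little. This is fair for that set, but the exclusion is itself selection on post-randomisation events, and the intention-to-treat analysis remains exposed.
- **Double entry.** It is not a further bias. It is a wording fault.

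None of this defends the model for the stated aim.

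**Conclusion.** The concern holds in conditional form. The primary ANCOVA, as published, adjusts for three variables that arise after randomisation. One group of them, pregnancy-induced diseases, is a declared outcome of the trial, and for gestational diabetes the Background describes both steps of a path to child BMI. If the programme changes any of these variables, the group coefficient does not estimate the total effect that the Discussion asks for, and shared causes can shift it further.

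The conclusion rests on the timing, which is certain, and on the possibility of a programme effect, which is written down for pregnancy-induced diseases and inferred for breastfeeding. Size and direction cannot be derived from the document. The range of 0.8–0.6 SD and 77–53% power is an illustration under assumed shares of 20–40%, not a forecast. Adjustment for parental age, paternal BMI and socioeconomic status is not in question. Because the point decides what the primary result means, the wording should be corrected before analysis.

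**What to change.** Reword the primary analysis in the Statistics section:

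1. Limit the ANCOVA of BMI at 24 months to group plus the listed variables that are fixed before randomisation: parental age, paternal BMI, socioeconomic status, and smoking as recorded at entry. Maternal pre-pregnancy BMI may be added as an option.
2. Remove breastfeeding (both entries), gestational diabetes and PIH from the primary model.
3. Keep pregnancy-induced diseases as the secondary outcome they already are.
4. Place any adjustment for these diseases or for breastfeeding in a separately labelled exploratory analysis, with the coding of breastfeeding stated once.

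The cost is a few lines of analysis wording. No change to data collection, recruitment or sample size follows from it.

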#### Drop-out criteria

Women with complications during pregnancy as assessed by participating obstetricians and physicians will be excluded from the study. Furthermore, women who will give birth pre-term (delivery before 37th week of gestation), who will not have participated regularly in the program (less then 80% of the units) or who will have missed blood tests (at the beginning of the program or 36th week of gestation) will be excluded.

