#### Sample size

Power analysis was done based on recommendations of weight gain in German children at 24 months after birth [37]. Normal weight gain (50th percentile) after subtraction of birth weight is nine kilograms at the age of 24 months. The BMI shows a difference of 1 kg/m^2^ at this time point (50th percentile). Therefore, a difference of 1 kg/m^2^ at the age of two years between the intervention and the control group will be assumed. To detect this difference in proportions with 80% power (GPower analysis) using a significance level of 0.05 and an effect size of 1.0, 48 women are needed. Calculating with a drop-out rate of 25% during the program, 60 women are required and planned to be recruited for this study.

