#### Primary outcome

The primary outcome of this study will be the BMI of the infant at two years after birth assessed by German percentile [44].

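### The primary BMI comparison is planned in both a per-protocol and an intention-to-treat population, each at alpha 0.05, and the protocol does not say which one decides

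*Protocol article*

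**What the plan says.** The section Primary outcome names a single endpoint: "The primary outcome of this study will be the BMI of the infant at two years after birth assessed by German percentile". The section Statistics gives it a single model: "The main variable (BMI at 24 months) will be analyzed by covariance analyses evaluated by the factor group, breastfeeding, and smoking", with further covariates. It then sets the error rate, "The significance level alpha will be set at < 0.05 for all analyses", and the populations, "Analyses will be carried out as per-protocol-analyzes and intention-to-treat analyses (ITT".

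No section calls either population primary, main, supportive or a sensitivity analysis. None sets a testing order or requires both results to be significant.

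Statistics does not define the per-protocol set. The only rules from which one could be built stand under Drop-out criteria. That section removes women "who will not have participated regularly in the program (less then 80% of the units", as well as women with pre-term delivery or missed blood tests, and it also states: "Women with complications during pregnancy as assessed by participating obstetricians and physicians will be excluded from the study". It describes this as leaving the study, not as leaving one analysis set.

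**The concern.** One endpoint is fixed, but the comparison that answers the trial's question is not. With two p-values for the same endpoint, both judged at 0.05, the choice between them can be made after the results are known.

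The two populations are not equally trustworthy. Every candidate rule for the per-protocol set is known only after randomisation, and one of them is adherence itself. If families who attend regularly would have had leaner children anyway, a set selected on attendance favours the programme even when it does nothing. Complications and pre-term birth may themselves be affected by the programme. The stated aim, whether the programme has an impact on infant BMI, is a superiority question, for which the randomised comparison is the one to rely on.

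The gap remains even if every infant is followed to 24 months: the deciding p-value would still be unnamed.

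**Working it through.** **Inputs from the protocol.** 30 women per arm (Intervention and Control group); alpha 0.05 (Statistics; two-sided assumed, since sidedness is not stated); 25% loss and a standardised effect of 1.0 (Sample size).

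**Assumptions, not in the protocol.** Retention of 60% (intervention) and 90% (control) as an unequal alternative to 75%/75%; correlation r = 0.2 to 0.3 between being retained in the intervention arm and lower child BMI; a smaller true effect of 0.6 SD; unadjusted t-tests with complete intention-to-treat outcomes, in place of the planned covariance analysis with last value carried forward.

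**Step 1: one deciding test.** With no true effect, intention-to-treat alone rejects in about 5% of simulated trials, which is the stated level.

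**Step 2: either test may be claimed, exclusions unrelated to BMI.** The per-protocol set is nested in the full set, so the two test statistics are strongly correlated.

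- 75% retained in both arms: 60 × 0.75 = 45 women, and ρ = √(45/60) = 0.866.
- 60%/90% retained: 30 × 0.60 = 18 and 30 × 0.90 = 27 women, and ρ = (2/30) / √[(2/30) × (1/18 + 1/27)] = 0.849.

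The chance that at least one test is significant is 1 − P(|Z₁| < 1.96 and |Z₂| < 1.96). At ρ = 0.866 this is 0.073, and at ρ = 0.85 it is 0.075. Simulation agrees at about 7.4% and 7.5%. The figure for two independent tests, 1 − 0.95² = 0.0975, does not apply because the tests share most of their data.

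**Step 3: either test may be claimed, adherence related to BMI.** Simulated null trials, 30 per arm, selection on outcome in the intervention arm only:

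| Retained (intervention/control) | r | Either significant |
|---|---|---|
| 75%/75% | 0.2 | about 8.3% |
| 75%/75% | 0.3 | about 9.3% |
| 60%/90% | 0.2 | about 9.5% |
| 60%/90% | 0.3 | about 11.9% |

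In the 60%/90% rows the per-protocol test alone rejects in about 7% and 9% of trials, while intention-to-treat stays near 5%. Most of the excess at r = 0.3 therefore comes from bias in the per-protocol comparison rather than from testing twice.

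**Step 4: how often the two analyses disagree when there is an effect.** With random exclusion at either retention pattern, one analysis is significant and the other is not in about 20 to 21% of trials at 0.6 SD, and in about 7.5 to 8.9% at the design effect of 1.0.

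**The case against.** **It can be left to the analysis plan.** Reporting both populations is ordinary practice, the article is condensed, and an analysis plan that is not shown may name the deciding set. This has some force. But the article is not silent on populations: it fixes two for its single primary outcome, side by side, each at the full 0.05. A later document would have to resolve an ambiguity that this text created.

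**Two chances of success.** A reader might infer that the trial may claim success if either analysis is significant. The protocol does not say so; its silence fits equally with requiring both, or with letting intention-to-treat lead. The error rates in steps 2 and 3 apply only under the reading that either suffices. That per-protocol is mentioned first carries no weight.

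**A doubled error rate.** A reader might put the error near 10% from two separate tests. The sets are nested with a correlation of about 0.85, so double testing alone gives 7 to 7.5%. Counting only false claims of benefit, it is about 3.8%, against a nominal 2.5%.

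**The per-protocol set is inferred.** This is correct. The 80% rule refers to units of the programme, which also includes nutrition counselling, and no section says that it applies to the control group's relaxation class. If the exclusions are applied literally, women leave the study altogether and the two sets largely coincide. That would reduce the disagreement, but only because the intention-to-treat analysis would then carry the same selection.

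**Blinded analysis.** Statistics says that the analysis will be blinded. Blinding hides the arms; it does not settle which of two p-values counts.

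**Conclusion.** The point stands as a gap in the stated primary analysis: two populations at full alpha, and no deciding one. Double testing by itself inflates the error modestly, to about 7 to 7.5% at the protocol's own 25% loss. The range of 8 to 12% depends on assumed retention and on an assumed link between adherence and child BMI, neither of which the protocol gives. Disagreement in one trial in five holds at 0.6 SD; at the effect that the trial was designed for it is 8 to 9%. All figures use unadjusted t-tests with complete intention-to-treat outcomes. None of them shows that a per-protocol claim is intended, only that the text leaves room for one.

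**What to change.** In Statistics, add:

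> The primary analysis is the difference between intervention and control in infant BMI at 24 months by intention-to-treat (all randomised women, in the arm assigned), at two-sided alpha 0.05. The trial's conclusion rests on this test alone. The per-protocol analysis is supportive and will not be used to claim efficacy.

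This cannot be carried out while Drop-out criteria removes women from the study for low attendance, complications, pre-term birth or missed blood tests. The two sections must be reconciled: the criteria should define the per-protocol set rather than removal from the study, and the 24-month infant records of those women should still be obtained where possible. This concerns data collection and analysis sets only, not whether a woman continues the programme.

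The cost is a wording change in two sections, plus collection of existing examination records for families who would otherwise be lost. Follow-up already takes infant weight and height from such records. No extra participants are needed. A significant per-protocol result could no longer be presented as the main finding.

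### Plain r-squared is named as the explained-variance statistic for multi-predictor regressions on about 45 to 60 children, so the reported figure will be inflated by the number of predictors

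*Protocol article*

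**What the plan says.** The Statistics section of the protocol article plans a set of secondary association analyses: "Multiple linear regressions will be performed for neonatal measures to determine correlations with maternal and paternal lifestyle factors". It then describes the other terms: "The model will include group (intervention yes/no) as well as maternal and paternal characteristics as possible confounders". The statistic to be reported for these models is given as follows: "Explained variance (r-squared) for the linear regression model will be reported as model fit statistic". Neither the number of predictors nor an adjusted version of the statistic is mentioned.

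The Sample size section sets the scale on which the models will be fitted: "48 women are needed" for the main comparison, and "Calculating with a drop-out rate of 25% during the program, 60 women are required". The inclusion criteria admit singleton pregnancies only, so there is one child per woman. Both per-protocol and intention-to-treat analyses are planned.

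**The concern.** Ordinary r-squared cannot fall when a term is added to a regression, even if the term is pure noise. In a large sample with few predictors this hardly matters. Here the sample is small and the model takes in several kinds of term: group, lifestyle factors of both parents, and characteristics of both parents. A visible part of the reported explained variance may then reflect how many terms were entered.

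What is at stake is interpretation. The Discussion says the findings should help to detect influential lifestyle factors and provide a basis for recommendations. A reader who sees a fifth of the variance in a neonatal measure labelled as explained will tend to take it as a finding, although a model with no real content could produce that value at this sample size.

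**Working it through.** **The plan's own figure.** The article gives no r-squared value and no predictor count, so there is none to reproduce. Its contribution is the sample size.

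**Inputs from the article**
- Upper n: 60 women recruited (Sample size), hence 60 children.
- Lower n: 25% drop-out (Sample size), 60 × 0.75 = 45.
- The stated evaluable number, 48, lies inside this range. How 48 and 60 were derived is a separate question. It enters here only through n.

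**Input assumed**
- Number of predictors p, excluding the intercept. One term of each kind named in the text (group, maternal lifestyle, paternal lifestyle, maternal characteristic, paternal characteristic) gives p = 5, and the wording is plural. A range of 8 to 12 is plausible if age, BMI, socioeconomic status, smoking, activity, diet and weight gain are used. I show 3 to 15.

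**Formula.** If no predictor has an effect and errors are normal, r-squared follows a Beta(p/2, (n-1-p)/2) distribution, so

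E[r²] = p/(n-1).

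For example, 8/59 = 13.6% and 12/44 = 27.3%.

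| p (assumed) | n = 60 | n = 48 | n = 45 |
|---|---|---|---|
| 3 | 5.1% | 6.4% | 6.8% |
| 5 | 8.5% | 10.6% | 11.4% |
| 8 | 13.6% | 17.0% | 18.2% |
| 10 | 16.9% | 21.3% | 22.7% |
| 12 | 20.3% | 25.5% | 27.3% |
| 15 | 25.4% | 31.9% | 34.1% |

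These are averages. The 5th to 95th percentile range with no effects is 4.9 to 25.0% for n = 60, p = 8, and 13.2 to 43.7% for n = 45, p = 12.

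**Adjusted r-squared.** The adjusted form is

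adjusted r² = 1 - (1 - r²)(n-1)/(n-p-1).

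Putting in the null mean for n = 45, p = 12: 1 - (1 - 12/44) × 44/32 = 1 - (32/44)(44/32) = 0. A simulation of 5,000 data sets with no effects agrees:
- n = 60, p = 8: mean r² 13.5%, mean adjusted r² -0.0005.
- n = 45, p = 12: mean r² 27.2%, mean adjusted r² -0.0005.

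**When something is explained.** With a true explained variance of 0.10 and n = 45, simulation (3,000 runs) gives:
- p = 8: mean r² 0.259, mean adjusted r² 0.094.
- p = 12: mean r² 0.340, mean adjusted r² 0.092.

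The adjusted form is thus close to the truth, though not exactly unbiased.

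**Share due to lifestyle factors.** The table is for all terms together. If k of the terms are lifestyle factors and nothing in the model has an effect, their expected share is k/(n-1). With an assumed k = 4 this is 4/59 = 6.8% to 4/44 = 9.1%. It is less if the other terms explain real variance.

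**The case against.** The strongest case against the point is that plain r-squared is an ordinary description of fit. It is, correctly, the share of variance explained in the fitted sample. The article presents it as a fit statistic for the model and attaches no test, threshold, model selection or model comparison to it. Coefficient tests and the overall F test use residual degrees of freedom, so this bias does not inflate them. An article condenses a fuller plan, and adjusted r-squared may be reported alongside.

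Most of this stands, and it limits the consequence. It does not remove the point. The article commits to one named statistic, labels it explained variance, and mentions no adjustment. A fuller plan could add the adjusted value, but the statement as published does not.

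A reader might go further in three ways that the document does not support:
- **That ineffective lifestyle factors will be reported as explaining about 14 to 27% of neonatal outcomes.** That range is for the whole model, including group and confounders, and it rests on an assumed 8 to 12 predictors. The article does not say r-squared will be credited to lifestyle factors.
- **That the covariate list for BMI at 24 months fixes p.** That list belongs to the primary covariance analysis. It only suggests which characteristics might be used in these regressions.
- **That larger models will be preferred because their r-squared is higher.** No such comparison is planned.

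**Conclusion.** The point holds as a minor one. At about 45 to 60 children, the named statistic overstates explained variance by an amount that depends on the number of predictors. With no true effects, the whole model is expected to show 8.5 to 11.4% for 5 predictors, 13.6 to 27.3% for 8 to 12, and 5.1 to 34.1% across 3 to 15. The sample sizes come from the article, and the predictor counts are assumptions. The bias shrinks as the true explained variance rises. The statistic is secondary and descriptive, and the primary analysis of infant BMI at two years and its group comparison are untouched.

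**What to change.** Replace the sentence on model fit with one that names adjusted r-squared as the explained-variance statistic, reported with the number of predictors and the number of children in each model. Plain r-squared may stay beside it.

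Wherever explained variance is to be attributed to lifestyle factors, fit the model with group and parental characteristics first, then add the lifestyle factors. Report the change in adjusted r-squared with the F test for that step. Negative adjusted values should be reported as they are.

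The cost is one sentence of wording and negligible analysis work, with no new data and no design change. The downside is that the reported explained variance will look less favourable.
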